### Study Procedure

The study procedure is outlined in Figure 1. All participants will complete the study questionnaires before the fMRI, 3 months after completing the IET, and 12 months after the fMRI. Questionnaires will be presented in paper form. Post-IET questionnaires will be sent to participants by paper mail. Questionnaires will be pseudonymized.

**Figure 1 figure1:**
[figure not shown]
The study procedure. fMRI: functional magnetic resonance imaging; IET: interoceptive exposure technique; LBP: low back pain; MRI: magnetic resonance imaging.

Participants at risk for LBP chronification will be classified and categorized within 48 hours after fMRI. High-risk participants will be further pseudo-randomized into the intervention (IET) or control group (A), whereas low-risk participants will form the treatment-as-usual group (B). Participants will be provided with group-specific instructions on the remaining study procedures by email and telephone. Participants in the intervention group will begin practicing the IET within a week after neuroimaging.

### Study Setting

The IET to be used in this study is a modified version of the IET used by Flink et al [31]. The original Swedish version used in the original study was translated into Finnish with small adjustments to the IET without departing from the structure and scope of the original exercise. At the beginning of the study procedure, the participants will be given brief information about the IET. The participants will access the IET through a web-based platform secured by a personal password and a username. The platform can be accessed on a mobile phone or a home computer with internet access. The participants will then be told to perform the 8 minutes and 26 seconds–long IET exercise 3 times a week (Monday, Wednesday, and Friday) in as serene a setting as possible. During the IET, the participants will be asked to relax and calmly focus their attention on the sensation of pain. They will be told to focus on the pain with an open and nonjudgmental attitude and to feel the pain as much as possible without trying to change it or block it. If their attention wanders from the pain, they will be asked to return their focus to the pain sensation. The web-based exercise platform will keep track of the participant’s activity. Platform visits and the time spent committing to the IET will be recorded. In this way, the research team can contact the participant if he or she is not logging on to the platform or if the IET is not carried out completely. The participant will be reached by phone to investigate the problem with attendance. If the participant misses 3 consecutive training sessions (ie, 1 week’s training), he or she will be excluded from the study. The IET intervention is designed to take 12 weeks. The IET exercise (in Finnish) is presented in Multimedia Appendix 1.

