### Aims and Objectives

There is a shortage of studies on interventions to prevent the chronicity of subacute back pain [25]. Considering the recent increase in knowledge about psychological risk factors, as well as recent findings in cognitive neuroscience regarding emotional and cognitive background factors in the LBP chronicity process, efforts should be made to discover effective preventive methods. Therefore, we will conduct a study aiming to prevent the chronicity of subacute LBP by altering the emotional response to pain using an interoceptive exposure technique (IET).

The aims of this study are as follows:

A pilot study will address the efficacy and feasibility of IET in preventing the chronicity of subacute pain. Participants who are found to have a higher risk of pain chronification due to the presence of a biomarker (functional mPFC-NAc synchronicity) will be randomized to the intervention group (n=7) or control group A (n=7; treatment as usual). To assess how well this biomarker predicts LBP chronification, participants who are not found to have the biomarker will be assigned to control group B (treatment as usual) without a defined number of participants.A full-scale study (intervention group: n=20; control group: n=20) will address the efficacy and feasibility of the IET in the prevention of subacute LBP chronicity with the same parameters as in the pilot study.

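### Excluding IET participants from the study after three consecutive missed sessions is a post-randomisation exclusion that only the IET arm can trigger; it exposes the comparison with control group A to selection bias of unknown direction and size and truncates the feasibility information.

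*Protocol article*

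**What the plan says.** Study Setting in the protocol article states: "If the participant misses 3 consecutive training sessions", which it equates with one week of training, "he or she will be excluded from the study". The exercise is scheduled three times a week, and "The IET intervention is designed to take 12 weeks". The same section says that the web platform logs visits and time spent on the exercise, and that the team telephones participants who do not log on or do not complete it.

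On timing, Study Procedure places classification and allocation of high-risk participants within 48 hours of the fMRI. It then says: "Participants in the intervention group will begin practicing the IET within a week after neuroimaging". Missed sessions can therefore occur only after allocation. Control group A receives treatment as usual, and no corresponding rule is stated for it.

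Aims and Objectives gives the purpose: "A pilot study will address the efficacy and feasibility of IET in preventing the chronicity of subacute pain". It plans 7 participants in each randomised arm for the pilot and 20 per arm for a full-scale study that keeps the pilot's parameters. The primary outcome is pain intensity on the NRS. Data Collection and Statistical Analysis compares the groups with mixed models and does not say what happens to participants excluded under the adherence rule.

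**The concern.** Randomisation makes the IET arm and control group A comparable at allocation. A rule that later removes people from one arm because of their behaviour undoes part of that. Those who remain in the IET arm are selected for adherence, while control group A has no sessions to miss and is not selected in this way.

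The behaviour is plausibly related to the primary outcome. The exercise asks people to attend to their pain, so those who get worse may stop. Those whose pain resolves may also stop. The first pattern would flatter IET and the second would work against it.

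The wording removes the person from the study, not only from the exercise. Questionnaires that are not collected cannot be restored by any later choice of analysis set. A pilot with a feasibility aim also needs to know what becomes of the people who do not keep up with the home exercise.

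**Working it through.** The article gives no power, SD, dropout or adherence figure behind 7 + 7 or 20 + 20, so there is no stated figure to reproduce. The steps below are an illustration.

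**Inputs from the article.** 3 sessions a week x 12 weeks = 36 sessions; exclusion after 3 consecutive misses; 7 per arm (pilot) and 20 per arm (full scale).

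**Assumed inputs.** Misses independent, at 10% to 30% per session; correlation rho between adherence and pain outcome of 0.2 to 0.6; no true IET effect; normal outcomes.

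**Step 1: chance of triggering the rule.** The probability q of at least one run of 3 misses in 36 sessions was computed exactly with a Markov chain on the current run length (0, 1, 2, excluded).

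**Step 2: shift in the IET mean.** If the least adherent fraction q is removed, the mean outcome of those remaining moves by rho x phi(c)/(1 - q), where c is the standard normal quantile at 1 - q and phi is the normal density. At a 20% miss rate, q = 0.201, c = 0.839, phi(c) = 0.281, and the factor is 0.281/0.799 = 0.351. The shift is then 0.2 x 0.351 = 0.07 SD to 0.6 x 0.351 = 0.21 SD.

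| Miss rate | q | Expected excluded of 7 | of 20 | Factor | Shift, rho 0.2 to 0.6 |
|---|---|---|---|---|---|
| 10% | 0.030 | 0.2 | 0.6 | 0.071 | 0.01-0.04 SD |
| 15% | 0.094 | 0.7 | 1.9 | 0.185 | 0.04-0.11 SD |
| 20% | 0.201 | 1.4 | 4.0 | 0.351 | 0.07-0.21 SD |
| 30% | 0.501 | 3.5 | 10.0 | 0.800 | 0.16-0.48 SD |

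The table gives the shift for one direction of selection. The sign reverses if those who recover are the ones who stop, and a mixture of the two partly cancels.

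The table counts any three misses in a row. If the rule means one whole Monday-to-Friday week, q = 1 - (1 - p^3)^12, with p the miss rate. This gives 1%, 4%, 9% and 28% at the four miss rates, and smaller shifts.

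**Step 3: comparison with precision.** With everyone retained, the 95% half-width for a difference in means is t x sqrt(2/n):
- 7 per arm: 2.179 x sqrt(2/7) = 1.16 SD.
- 20 per arm: 2.024 x sqrt(2/20) = 0.64 SD.

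A shift of 0.07-0.21 SD is 6-18% of the first half-width and 11-33% of the second.

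**Step 4: type I error.** Two-sided t-tests at 0.05, 40,000 simulated trials per scenario, no true effect, selection in one direction:

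| Per arm | Excluded from IET | rho | Bias (SD) | Type I error |
|---|---|---|---|---|
| 7 | 2 | 0.5 | -0.21 | 0.066 |
| 7 | 2 | 0.7 | -0.30 | 0.080 |
| 20 | 4 | 0.5 | -0.17 | 0.081 |
| 20 | 6 | 0.5 | -0.24 | 0.106 |
| 20 | 6 | 0.7 | -0.33 | 0.170 |

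With everyone kept in the allocated arm, the bias is 0.00 SD and the type I error 0.049-0.051 in every scenario.

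**The case against.** The strongest defence is that the damage to the pilot is limited and that the article already keeps useful adherence data. Much of that stands, and it rules out several stronger readings.

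- *Feasibility is erased.* A reader might infer this, but Study Setting records platform visits and time and has non-attenders telephoned. The number excluded, when, and the attendance problem found can be reported against all randomised to IET. What is lost is what happens to those people afterwards.
- *The comparison is biased in favour of IET.* The article does not support a direction. Worsening and recovery are both plausible reasons to stop.
- *Control group A stays complete.* It need not. Participant Selection lets anyone withdraw without giving a reason, and the exclusion after lumbar MRI is not tied to an arm. Only the adherence rule is one-sided.
- *The bias is large.* Large shifts need high miss rates and strong correlations. At 10% missed the shift is at most about 0.04 SD. The telephone contact may interrupt runs of misses, while clustering of misses would make them more common.
- *The lack of an intention-to-treat statement is itself the error.* It is not, because a condensed article may leave analysis sets to a fuller document.

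This last point does not rescue the rule. The article states the exclusion outright, and an analysis plan cannot recover outcomes that were never collected. Study Procedure does say that all participants complete the questionnaires, but it does not say that excluded people still count as participants. If that was intended, the two sections need to be reconciled.

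**Conclusion.** The point holds as an exposure to bias and a loss of data, and the rule should be changed before enrolment. As written, it is a one-arm, adherence-based exclusion after randomisation. The plausible size runs from negligible (0.01 SD at 10% missed, rho 0.2) to substantial (0.48 SD at 30% missed, rho 0.6). It rests on assumed miss rates, independence of misses and assumed correlations.

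In the pilot, imprecision dominates. The consequence is greater at 20 per arm, provided that the exclusion rule is among the parameters carried over from the pilot.

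**What to change.** Replace exclusion from the study with recording three consecutive missed sessions as a non-adherence event. This concerns follow-up and analysis only, not whether the person goes on with the exercise. Then:

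- keep mailing the post-intervention and 12-month questionnaires to everyone randomised, unless they withdraw;
- analyse all high-risk participants in the arm to which they were randomised;
- report the number and proportion meeting the three-missed-sessions rule, out of all randomised to IET, as a feasibility outcome;
- make any adherers-only analysis supplementary.

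The cost is a change of wording and a few more mailed questionnaires. The estimate will describe the effect of being assigned to IET, diluted by non-adherence. The article reports no enrolment as of September 2023, so at that date the change could still cover every participant.

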### Outcome Assessment and Measurements

The questionnaires used in the study will address conditions of pain experience and psychological distress. All measures are standardized and commonly used in pain research.

For all visits, participants will complete the short form of the Finnish version of the McGill Pain Questionnaire (MPQ), abbreviated as the FPQ [32]. The main component of the MPQ consists of 12 sensory and 4 affective descriptors, which are used to compute the sensory and affective scores, respectively. Radiculopathy scores are quantified from pain locations, which patients shade in with pencil on the MPQ form 15. Depression scores are assessed using the BDI-II [27]. All questionnaires will be given on the same day before brain scanning. The questionnaires are presented in Textbox 1.

Behavioral measures and corresponding questionnaires to be used in the study, with abbreviations in brackets.
**Measures and corresponding questionnaires**
Pain intensity: Numeric Rating Scale (NRS) [26]Pain experience: the Finnish Version of the McGill Pain Questionnaire (FPQ) [32]Pain-related anxiety: Pain Anxiety Symptoms Scale (PASS-20) [33]Anxiety symptoms: State-Trait Anxiety Inventory (STAI) [34]Fear of movement: Tampa Scale of Kinesiophobia (TSK) [35]Depression: Beck Depression Inventory-II (BDI-II) [27]

Pain intensity will be estimated with the numeric rating scale (NRS), with a pain intensity ranging from “no pain” to “worst pain” (1-10) according to the conventional use of the NRS [26]. The subjective unpleasantness will be measured analogously on the NRS, ranging from “not unpleasant” to “extremely unpleasant.” The primary outcome will be pain intensity on the NRS. Secondary outcomes will be pain experience [32], pain-related anxiety [33], state and trait anxiety [34], fear of movement [35], and depressive symptoms [27] (Textbox 1).

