Recent brain imaging studies have further supported the role of emotional factors in the LBP chronification process, revealing mental factors influencing pain conditions [10]. Even in acute pain states, emotional factors seem to directly influence neural pain processing, as shown in the brain imaging study by Orenius et al [11], in which a valence-independent emotion interacted with the pain processing in the secondary somatosensory cortex. Functional and emotional nonadjustment factors have been identified in the acute LBP chronification process [12], with emotional nonadjustment relating to helplessness and hopelessness. Furthermore, chronification does not simply implicate the presence of enduring pain symptoms; it signifies a complex process associated with alterations in cortical structure and function. Vachon-Presseau et al [13] emphasized the importance of the emotional brain (ie, the cortico-limbic system) in the modulation of acute pain and in the prediction and amplification of chronic pain. A functional magnetic resonance imaging (fMRI) study showed that chronification of LBP shifts brain representation from nociceptive to emotional neural circuits [14]. These findings indicate the pivotal role that the neural structures involved in emotional learning play in the chronification of back pain [15]. Furthermore, the strength of synchronicity (ie, functional connectivity) between the medial prefrontal cortex (mPFC) and nucleus accumbens (NAc) was predictive (with >80% accuracy) of individuals who would subsequently transition from subacute pain to chronicity at a 1-year follow-up [15].

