## Methods

### Participant Selection and Sampling Strategy

All participant recruitment will take place through the pain clinic at the Orton Orthopaedic Hospital and another private occupational health center. All study participants will be outpatients at the pain clinic and the private occupational health center. They are working-aged Finnish citizens who speak Finnish as their first or second language. A health care professional will diagnose the participants’ back pain and assess them based on the inclusion and exclusion criteria.

The inclusion criteria approximately correspond to those of Baliki et al [15]: pain intensity >40/100 on the numeric rating scale (NRS) [26] and back pain duration <16 weeks. Deviating from the abovementioned criteria, we limit the pain duration time more precisely (ie, to 4-10 weeks) to enable commencement of the IET before exceeding the valid 12-week time limit for pain chronicity. Additionally, it will be implied that participants experience at least occasional back pain when lying on their backs. Exclusion criteria resemble those of Baliki et al [15]: other chronic painful conditions, systemic disease, history of head injury, psychiatric diseases, or more than mild depression (score >19), as defined by Beck Depression Inventory-II (BDI-II) [27]. As an addition, exclusion criteria also include self-reported earlier diagnosed prolonged LBP episodes and longer sick leaves due to LBP.

A health care professional (physician or physiotherapist) will ask patients with subacute back pain if they are willing to participate in the study. When a patient is willing to participate, the research secretary will contact the patient and check that he or she meets the research criteria. Then, the health care professional will provide the patient with information about the study procedure and deliver the information and a consent form to the patient, who will sign the consent document. The patient will be told that he or she has the right to stop his or her participation at any time without having to explain the reason. The participant, accompanied by the research secretary, will undergo an fMRI scan and fill out the questionnaires. The feedback from the lumbar magnetic resonance imaging (MRI) will be given to the participants by the clinician. If necessary, proper further examinations and treatments will be provided, and the participants will be excluded from the study.

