### Data Collection and Statistical Analysis

Data will be obtained before the fMRI, 3 months after completing the IET, and 12 months after the fMRI. Data will be compared between the groups (IET vs treatment as usual in control groups A and B). The data will be analyzed using a repeated-measures analysis (mixed models).

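### Both aims concern transition to chronic pain, but the stated outcomes and comparison give only a mean pain difference, with no chronification result and no biomarker analysis

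*Protocol article*

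**What the plan says.** Under Aims and Objectives, the efficacy aim reads "A pilot study will address the efficacy and feasibility of IET in preventing the chronicity of subacute pain". The second aim reads "To assess how well this biomarker predicts LBP chronification, participants who are not found to have the biomarker will be assigned to control group B". A later full-scale study with 20 per group is to keep the pilot's parameters.

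Under Outcome Assessment and Measurements, "The primary outcome will be pain intensity on the NRS", and Principal Findings repeats this. The secondary outcomes are scores for pain experience, pain-related anxiety, state and trait anxiety, fear of movement and depressive symptoms.

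Under Data Collection and Statistical Analysis, "Data will be obtained before the fMRI, 3 months after completing the IET, and 12 months after the fMRI". The stated comparison is IET against usual care in groups A and B, by repeated-measures mixed models. Only IET and A are randomized. B consists of biomarker-negative participants, with no set number.

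The background gives the biomarker claim: connectivity "was predictive (with >80% accuracy) of individuals who would subsequently transition from subacute pain to chronicity at a 1-year follow-up". Biomarker positivity is defined as z(r) ≥0.25. The Results section says the design allows the biomarker's validity to be replicated.

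**The concern.** Each aim names an event, yet no listed outcome records that event. The predictor has a cut-off, but what it predicts has no threshold, duration rule or status at follow-up. Sensitivity, specificity and accuracy all need a yes/no outcome, and the contrast that bears on the biomarker aim, A versus B, is not among the stated comparisons.

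Two things are at stake. A lower mean NRS in the IET group could be reported as prevention of chronicity without any count of chronic cases. And if a chronification status is derived later, its cut-off could be chosen after the data are seen. Because the full-scale study inherits the pilot's parameters, the gap would carry forward.

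**Working it through.** The article gives no alpha, effect size, SD or event rate, so there is no planned figure to reproduce. The main check sets aims against outcomes. The calculations that follow are illustrations, and their inputs are assumptions unless marked as coming from the article.

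**1. Aim against outcome**

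| Aim | What it needs | What is stated |
|---|---|---|
| IET prevents chronification | Chronification status, IET v A, at a named time | NRS intensity, two unranked follow-ups, IET v A and B |
| Biomarker predicts chronification | Chronification status in biomarker-positive and biomarker-negative participants under usual care | Questionnaire scores; no A v B comparison and no accuracy measure |

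**2. Dependence on the cut-off.** Assume 12-month NRS is normal with SD 2.5 and means 3.5 (control) and 2.5 (IET). The chronic share at cut-off c is 1 − Φ((c − mean)/2.5).

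- c = 3: 1 − Φ(−0.2) = 58% v 1 − Φ(0.2) = 42%
- c = 4: 1 − Φ(0.2) = 42% v 1 − Φ(0.6) = 27%
- c = 5: 1 − Φ(0.6) = 27% v 1 − Φ(1.0) = 16%

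The same mean difference of 1 point gives control rates from 58% down to 27%.

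**3. Scale.** Entry uses pain >40/100, while the outcome NRS runs 1-10 with no pain at the bottom. A linear conversion puts the entry level at 4 on a 0-10 scale (10 × 0.4) but at 4.6 on a 1-10 scale (1 + 9 × 0.4). On a 1-10 scale, pain-free is 1, so a rule for any pain must be >1; a rule of ≥1 would count everyone.

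**4. Precision.** The 7 and 20 per arm come from the article; two-sided alpha 0.05 is assumed.

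- Mean score (noncentral t): 80% power needs a standardized difference of about 1.64 with 7 per arm and 0.91 with 20.
- Binary status (exact power of Fisher's test, summing binomial probabilities over tables with p ≤0.05), assuming 80% v 40% chronic: about 15% with 7 per arm and 65% with 20.
- If 6 of the 7 in group A became chronic, the predictive value of a positive biomarker would be 86%, with an exact 95% interval of 42% to 99.6%.

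**5. Sampling of biomarker-positive participants.** The pilot sends 7 of 14 to IET, so group A holds half of them, while B holds all the biomarker-negative participants. With a chronic cases in A and b in B, pooled sensitivity a/(a + b) understates the screened population's value whenever both are above zero. Weighting A by 14/7 = 2 gives 2a/(2a + b). Specificity and overall accuracy need the same weight. Positive and negative predictive values do not.

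**6. Timing of the middle visit.** The Abstract places it after the intervention at 3 months, about week 13 after fMRI. Study Procedure and Data Collection and Statistical Analysis place it 3 months after IET is completed: up to 1 + 12 + 13 = 26 weeks after fMRI. The two readings differ by about 3 months.

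**The case against.** A continuous primary outcome is defensible with 7 per arm, and step 4 shows how little a binary outcome would tell about efficacy in the pilot. NRS at 12 months after fMRI is collected in all groups, which matches the horizon of the cited biomarker result. Prediction could also be studied by relating z(r), or A v B, to the 12-month score, and a three-group mixed model contains an A v B contrast. The full protocol or SAP may rank the time points and contrasts.

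Most of this stands, and it is why NRS should stay primary. It does not close the gap. The article lists its outcomes and its comparison, and none of them is the event named in both aims. A mean-score contrast does not reproduce a classification result.

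Three stronger readings are tempting, and the documents do not support them.

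- A reader might infer that neither aim can be answered at all. That is true of the stated outcomes only; a status can be derived from the scheduled data.
- A reader might infer that the 12-week limit is unusable as a definition because every participant passes it before IET ends. That treats weeks since onset as persisting pain. Some participants may recover, both follow-ups fall after the limit, and the article uses it only to time the start of IET: "to enable commencement of the IET before exceeding the valid 12-week time limit for pain chronicity".
- A reader might infer a specific inflated false-positive rate from two visits and two comparators. The plan names a mixed model, which can give a single test. It states no alpha and no rule that any one result suffices, and it sets no size for B.

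**Conclusion.** The concern holds as a mismatch between the aims and the stated outcomes and comparison. Following the article yields a mean NRS comparison, no chronification result and no biomarker analysis. This goes beyond detail that a SAP would ordinarily supply, because closing it means adding an outcome and a contrast. The unranked visits and the two descriptions of the middle visit add to it.

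No single number measures the gap. The illustration shows a control chronic share between 27% and 58% for cut-offs of 5 and 3, under the assumed normal distribution, means and SD. The change is worth making now: the article reports no enrolment as of September 2023.

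**What to change.** 1. Prespecify a binary chronification status at 12 months after fMRI, derived from the NRS with one cut-off fixed in advance, for example the trial's entry level. Use any persistent LBP as a sensitivity definition. First reconcile the >40/100 entry scale with the 1-10 outcome scale.
2. Use that status in groups A and B, both on usual care, to estimate the biomarker's sensitivity, specificity and accuracy with confidence intervals. Weight A for the half of biomarker-positive participants randomized to IET, and report predictive values alongside. Leave the IET group out, since treatment may change the outcome. Report the status for IET versus A as a descriptive secondary outcome.
3. Keep NRS intensity as the primary outcome. Name the randomized contrast IET versus A at 12 months as the primary estimate from the mixed model, with the earlier visit secondary. Reconcile that visit's timing between the Abstract and the two Methods sections.

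The cost is wording in the protocol, with no new visits or questionnaires. The earlier visit loses equal standing, and the binary outcome will be imprecise with 7 per arm, so it should be presented as estimation and not as a test of efficacy.
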